**Methods:**

This is an efficacy study using a randomized controlled trial design. HMZ 2.0 is a multidosage, theoretically based, and individually tailored adaptive intervention that is delivered through a novel digital platform with an automated link of participant data to a new model-based predictive control algorithm to predict GWG. Our new control system computes individual dosage changes and produces personalized physical activity (PA) and energy intake (EI) strategies to deliver just-in-time dosage change recommendations to regulate GWG. Participants are 144 pregnant women with overweight or obesity randomized to an intervention (n=72) or attention control (n=72) group, stratified by prepregnancy BMI (<29.9 vs ≥30 kg/m^2^), and they will participate from approximately 8 to 36 weeks of gestation. The sample size is based on GWG (primary outcome) and informed by our feasibility trial showing a 21% reduction in GWG in the intervention group compared to the control group, with 3% dropout. Secondary outcomes include PA, EI, sedentary and sleep behaviors, social cognitive determinants, adverse pregnancy and delivery outcomes, infant birth weight, and implementation outcomes. Analyses will include descriptive statistics, time series and fixed effects meta-analytic approaches, and mixed effects models.

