## Methods

### HMZ 2.0 Intervention Description

HMZ 2.0 is a multidosage, individually-tailored, adaptive intervention with social cognitive theory and behavior components [15-17]. The “baseline dosage” is delivered to all intervention participants, and it consists of up to 24 weekly modules (depending on gestational age at study enrollment) including the following:

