The staff member reviews the participant’s responses to determine eligibility. The inclusion criteria are as follows: age range 18-45 years; singleton pregnancy with ≥8 and <18 weeks gestation; any parity; any race or ethnicity; BMI of 24-45 kg/m^2^ (>40 with provider consent); have not gained >25% of total GWG (based on BMI and IOM guidelines) from prepregnancy to the date of enrollment [103]; able to read or understand English; access to a computer or phone; able to attend sessions either on-site or remotely; randomization to conditions; no absolute contraindications to PA (and presence of relative contraindications only with health care provider consent to participate); and not a current heavy smoker (>20 cigarettes per day) [19,69-71] . The exclusion criteria are as follows: outside the age, BMI, gestation, or GWG range; not able to participate (cannot read or understand English, no access to a phone or computer to attend sessions remotely, and cannot use a device or service assistance); absolute contraindications to PA [69-71] or relative contraindications to PA noted by the participant’s health care provider as precluding study participation; current heavy smoker (>20 cigarettes per day) at study entry; and multiple pregnancy. Eligible women are scheduled for the preintervention assessment. Women not meeting the eligibility criteria are thanked for their time and given information on other studies that may be of interest.

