### Control Optimization Trial Procedures

Control systems methodology [51-54] in a novel Control Optimization Randomized Controlled Trial (RCT) [51] is used to test the efficacy of the enhanced HMZ 2.0 intervention with a novel digital platform and a new automated control system to regulate GWG and influence secondary outcomes. This idiographic approach uses individual dynamic models (integrating behavioral and energy balance models) informing how each woman responds to HMZ 2.0 to make personalized decisions about intensifying dosages to regulate GWG. We are not aware of any other studies using this unique strategy to regulate GWG. Women start the intervention with an “open-loop” experimentation phase and receive the HMZ 2.0 baseline intervention (dosages are not yet adapted during this time). Semiphysical models estimated using concepts from system identification [85,118-120] allow individual energy balance and behavior models to be built for each subject [51]. Model and dosage personalization is further enhanced by leveraging our team’s expertise in time-varying dynamic systems (systems that show changes in statistical properties over time) and multilevel models that integrate individual- and group-based dynamics and missing data issues [56-68]. Model components are measured with real-time data procedures to predict corresponding deviations from each woman’s target GWG range: overweight, 6.8-11.3 kg total and 0.23-0.32 kg/wk; obese, 5.0-9.1 kg total and 0.18-0.27 kg/wk [1,2]. Model estimation is used to confirm individual models and identify if certain constructs provide maximum impact for the control system. The goal of this open-loop phase is to arrive at a set of personalized dynamic models that capture the effects of dosage augmentations, gestational age, and the baseline intervention. Once the models are identified and the controller commissioned, models will not be updated, but the tuning parameters can be adjusted, if necessary. While there is no set threshold of data compliance for building individual models (models can be built with as little as 50% missing data handled with maximum likelihood estimation) [56-68], we will rely on strategies to achieve high compliance (90%; 10% missing data) similar to that in our feasibility study [19].

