### Primary Outcome

#### Participant GWG

Weight and GWG are assessed daily at preintervention, during the intervention, and at postintervention at home using the Fitbit Aria Wi-Fi Smart Scale [112] (weights are wirelessly uploaded to an online program). GWG is standardized, and the target weight gain is determined for each woman based on the BMI status (overweight, 14.1-22.7 kg; obese, 11.3-19.1 kg) [1,2]. For the criterion measure to determine when to adapt the intervention, weight gain is calculated to determine if a woman is gaining less than her goal, at the exact amount of her goal, or more than her goal. GWG over the course of the study is calculated as the last measured weight during the study subtracted by the first measured weight during the study. Weight at enrollment is measured, and prepregnancy weight and GWG from the first prenatal visit to the last predelivery weight are abstracted from clinical records.

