
### Statistical Analysis

For study aims 1 and 2, time series methodology will be used on a subject basis (ie, cubic polynomial spline 3-lag auto-regressive models with maximum likelihood as the estimation method) followed by a fixed effects meta-analytic approach to combine information in order to compare the intervention group to the control group [141-143]. Mixed effects models will be used when the meta-analytic approach does not fit the data [56,62-65]. Potential confounding variables (eg, maternal age, parity, and income; infant sex; and adverse maternal-infant outcomes) [6,144] will be included in the models as covariates when appropriate. We will explore the extent to which prenatal sleep and eating behaviors impact postintervention GWG, PA, or EI and infant birth weight to inform modifications to the maternal energy balance and infant birth weight models. The intent-to-treat principle will be followed. Our statistical approach is robust if data are missing at random (multiple imputation will be considered if missing data are problematic) [145]. Hypothesis tests will invoke a 2-sided significance level of .05. Analyses for the synthesis of mHealth data and the predictive control system are informed by MATLAB toolkits and past experience [51,146,147]. Model personalization will use control-theory models, and requisite computations will be performed for optimal dosage changes [112,113,128,148-150]. For study aim 3, descriptive statistics will be used to examine the percentage and frequency for implementation markers. Formative methods will be used to organize, code, and rank order interview data [136,137]. Study findings will be used to further optimize HMZ 2.0 for effectiveness and scalability. Data will be collected and stored in REDCap [88]. Deidentified data will be exported from REDCap [88] to statistical packages. Subject confidentiality will be maintained with subject IDs. Data security is ensured with Penn State standard procedures.

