### Power Calculations

The primary outcome is GWG: absolute difference between the intervention and control groups for the mean change in GWG from the start to the end of the trial. From our feasibility study [19], we found that the difference between the intervention and control groups with respect to the absolute mean change in GWG from the start to the end of the trial was 1.9 kg (SD 4.9 kg), with an approximately 21% relative reduction for the intervention group compared to the control group. We compared the mean change in our feasibility trial [19] to that in several other GWG studies comparing intervention and control groups [29,151-154] and found that the intervention group gained on average 1.8 kg less than controls (range: 1.1-3.1 kg). The sample size of 144 randomized to the intervention (n=72) and control (n=72) groups in the proposed research is informed by our feasibility trial showing a mean difference of 1.9 kg (SD 4.9 kg), a 21% relative reduction in GWG in the intervention group compared to the control group, and a 3% dropout. Given our experience with the feasibility trial [19], the series of refinements that we performed following the feasibility trial (eg, adding content on sleep and eating behaviors given their effects on GWG; modifying all content for remote delivery given 100% compliance found for remote sessions in the feasibility trial; replacing the initial control system to make dosage change decisions with the new, automated, dynamic model-based predictive control system that outperformed the initial system for regulating GWG; and adding the novel HMZ 2.0 digital platform to adapt dosages), and the findings from our HMZ 2.0 pilot study (average weekly GWG over the 4-week study period: 0.3 kg, SD 0.4 kg; overall GWG from pre- to postintervention: 1.2 kg, SD 0.8 kg), we expect the HMZ 2.0 intervention to be more effective. We anticipate that our mean difference will be closer to what a recent study [155] found for the mean difference in GWG between the intervention and control groups (mean 3.6 kg, SD 5.7 kg). Conservatively, considering this larger SD of 5.7 kg and anticipating a larger dropout rate of 10%, the sample size of 144 yields 80% statistical power with a 2-sided significance level of .05 to detect an absolute difference of at least 2.9 kg in GWG between groups. Sample sizes for semistructured interviews are adequate to observe data saturation [136,137,141].

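### Primary weight gain is last minus first measured weight, so a woman whose weights stop early is scored as a low gainer, and nothing stated replaces that value

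*Protocol article*

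**What the plan says.** Under Participant GWG, the Protocol article gives the calculation rule: "GWG over the course of the study is calculated as the last measured weight during the study subtracted by the first measured weight during the" […]. Power Calculations makes the primary quantity the "absolute difference between the intervention and control groups for the mean change in GWG from the start to the end of the trial".

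The length of observation varies. Recruitment admits a "singleton pregnancy with ≥8 and <18 weeks gestation", and the abstract's Methods say of the women that "they will participate from approximately 8 to 36 weeks of gestation". The intervention description confirms the variation: "up to 24 weekly modules (depending on gestational age at study enrollment").

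Participant GWG also says that "GWG is standardized, and the target weight gain is determined for each woman based on the BMI status". The article does not explain the standardization, and the sentence goes on to BMI-based targets, not to time observed.

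Statistical Analysis plans per-subject time series followed by a fixed effects meta-analysis, mixed effects models where that does not fit, and intention to treat. On missing data it assumes missing at random and adds that "multiple imputation will be considered if missing data are problematic". Neither gestational age at entry nor time observed is among its example covariates, and randomization is stratified by prepregnancy BMI only.

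**The concern.** Using whichever weight came last as the final weight carries the last observation forward, and here the direction of the error is known. A woman who gives no weights after, say, 24 weeks is credited with her gain to 24 weeks as if it were her gain to the end of the trial. She has a number, so under that rule nothing about her is missing and imputation has nothing to act on.

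If such women are spread evenly over the arms, the damage is a diluted effect. If there are more of them in one arm, that arm shows a lower mean gain for a reason unrelated to treatment. The trial tests for lower gain, so more stopping in the intervention arm would look like efficacy, and more stopping in the control arm would hide it. The contact schedules do differ: weekly modules plus step-ups against four weekly sessions followed by monthly videos and check-ins.

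The entry window is a second, lesser matter. Women followed for different lengths of time have different expected gains, and the stated rule does not adjust for this.

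**Working it through.** **Inputs from the article.** Entry at 8 to <18 weeks (Recruitment); end at about 36 weeks (abstract, Methods); 72 per arm (Randomization Procedures); SD 5.7 kg, dropout 10%, two-sided 0.05, 80% power, detectable difference 2.9 kg (Power Calculations); guideline rates "overweight, 6.8-11.3 kg total and 0.23-0.32 kg/wk; obese, 5.0-9.1 kg total and 0.18-0.27 kg/wk" (Control Optimization Trial Procedures).

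**Assumptions.** Entry uniform over 8 to 18 weeks. Stopping at a random time, so on average half the window is lost. Dropout of 15% in one arm and 5% in the other, which averages the planned 10%. No true effect when bias is computed. The rate of 0.40 kg/wk is an upper illustration that the article does not give.

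**1. The plan's own figure.** Evaluable per arm: 72 × 0.9 = 64.8. Detectable difference: 5.7 × √(2/64.8) × (1.960 + 0.842) = 2.81 kg by the normal approximation, 2.83 kg by the t-test. Power at 2.9 kg is 82.5% and 82.0% respectively. The stated 80% is reproduced to within about 2 to 3 points and does not depend on this concern.

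**2. Observation windows.** 36 − 18 = 18 weeks to 36 − 8 = 28 weeks; the mean is 36 − 13 = 23 weeks.

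**3. One early stopper.** Stopping halfway loses 23/2 = 11.5 weeks. Her gain is understated by 11.5 × 0.18 = 2.1 kg to 11.5 × 0.32 = 3.7 kg.

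**4. Bias with unequal dropout.** Spurious difference = (difference in dropout) × (weeks lost) × (weekly rate). For the type I error, SE = 5.7 × √(2/72) = 0.95 kg, since under the stated rule every woman with two weights has a value.

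| Rate (kg/wk) | Spurious difference (kg) | Share of 2.9 kg | Two-sided type I error |
|---|---|---|---|
| 0.18 | 0.10 × 11.5 × 0.18 = 0.21 | 7% | 5.5% |
| 0.32 | 0.10 × 11.5 × 0.32 = 0.37 | 13% | 6.7% |
| 0.40 (assumed) | 0.10 × 11.5 × 0.40 = 0.46 | 16% | 7.7% |

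With wider assumptions (dropout differing by 5 to 20 points, last weight 9 to 20 weeks early, 0.18 to 0.32 kg/wk) the range is 0.05 × 9 × 0.18 = 0.08 kg to 0.20 × 20 × 0.32 = 1.28 kg.

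**5. Equal dropout.** With 10% in each arm and half the window lost, a true effect that builds up evenly over time shrinks by 0.10 × 0.5 = 5%.

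**6. Unequal entry.** The SD of entry time is 10/√12 = 2.89 weeks, which adds an SD of 2.89 × 0.18 = 0.52 kg to 2.89 × 0.32 = 0.92 kg. If none of this is already in the 5.7 kg, the total SD is √(5.7² + 0.52²) = 5.72 to √(5.7² + 0.92²) = 5.77 kg. Power at 2.9 kg falls from 82.5% to between 82.2% and 81.6%, a loss of under 1 point. Randomization balances entry time in expectation, so there is no bias.

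**The case against.** The strongest reply is that the change score may not be what is analysed. Statistical Analysis assigns the GWG aim to models of repeated measurements, and a mixed model on daily weights would handle early stopping under missing at random. A reader might infer from the last-minus-first rule that the missing-data provisions can never apply. The article does not support that: the models are planned, and the power calculation treats the 10% who drop out as lost. Change to the end of the trial could also be read as requiring an end-of-trial weight.

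A reader might also infer that the trial is biased in favour of the intervention. That is not shown either. The 15% versus 5% split is an assumption. The feasibility trial reported 3% attrition among 31 women, both arms follow the same measurement protocol, and a woman who must stop physical activity stays in the study and completes measures as appropriate. Higher dropout among controls would bias the result the other way.

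Finally, prenatal records give gain to the last predelivery weight, and a condensed article may leave detail to a fuller document.

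These points limit the size and certainty of the problem. They do not remove it. The article does not omit the rule; it states one, and that rule gives an early stopper a wrong final value. Nothing in the article says that the models, the unexplained standardization or the record-based total override it, and the power section is written for the raw mean change.

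**Conclusion.** The concern holds for early stopping. As stated, the primary outcome understates gain for any woman whose weights end early, and it favours whichever arm has more such women. At the article's guideline rates, with the assumed 15% versus 5% dropout and stopping halfway on average, the spurious difference is 0.21 to 0.37 kg; at an assumed 0.40 kg/wk it is 0.46 kg. That is too small to create a 2.9 kg difference by itself, but it is systematic and avoidable. With equal dropout the only cost is the 5% attenuation. The 18- to 28-week windows are a matter of precision, not validity, and would not justify a change alone. This should be fixed. It is an unresolved conflict between a stated outcome rule and the planned models, not a demonstrated bias in this trial.

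**What to change.** Replace the last-minus-first rule for the primary outcome with the difference between arms in weight gain from baseline to a fixed gestational age. The plan's own end, about 36 weeks, is the natural choice. Estimate it from the daily Aria scale weights with the mixed effects model that Statistical Analysis already names, adjusted for baseline weight, gestational age at entry and BMI stratum. State that all recorded weights are used under intention to treat, that weights not recorded after a woman stops are missing, and that her last weight is never taken as her final one. Use the same definition in Participant GWG, Power Calculations and Statistical Analysis, and say there what the standardization of GWG means.

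The cost is wording in the outcome and analysis sections. No new data are needed, since daily weights are planned in both arms, and only 12 women were enrolled when the article was written. The mixed model would become the primary analysis of GWG where it is now the fallback. The price is reliance on missing at random, which the article already assumes.

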#### Energy Balance and Behavior Model Primary Constructs

##### PA and Sedentary Behavior

PA and sedentary behavior are assessed daily at preintervention, during the intervention, and at postintervention. Participants wear the wrist-worn Fitbit Charge 6 [112] 24 hours per day from the preintervention assessment until the end of the postintervention assessment. The Fitbit Charge 6 allows for continuous passive (low subject burden) PA assessment in the energy balance model [12] to predict GWG. The device measures total kcal, activity kcal, steps, and minutes in sedentary, light, or moderate PA. The waist-mounted ActiGraph GT3X [123] is worn at pre- and postintervention and for the first 2 weeks of the open-loop phase during waking hours to assess PA and sedentary behavior (activity kcal, steps, and minutes in sedentary, light, or moderate PA). Participants track their PA and monitor wear time by completing a self-report PA log and the Leisure Time Exercise Questionnaire [124] daily for cross-validation of the Fitbit data [125].

##### EI Behavior: Back-Calculation Estimation

EI is estimated daily at preintervention, during the intervention, and at postintervention from measured weight (Aria Wi-Fi scale) [112], PA (Fitbit Charge 6 activity monitor) [112], and resting metabolic rate (RMR), with k=1, 2,… N relating to day 1 to day N. T is the sampling time (T=1 day) [8,12,68-71], and RMR is estimated daily as follows:

eRMR = 0.1976W^2^ – 13.424W + 1457.6 **(1)**

The noise in weight is small relative to the total weight, but the extent of this noise can affect the calculated rate of GWG per day, so a 5-day moving average filter is used to preprocess (smooth) measured weight before “true” daily EI is estimated [117-119]:

Our team effectively used this back-calculation method for estimating EI in the HMZ proof-of-concept study [42] and feasibility-initial impact randomized trial [8,10,19,43-45].

### Secondary Outcomes

#### Secondary Energy Balance and Behavior Model Constructs

The following aspects are considered:

Theory of Planned Behavior [15,126]: Involves healthy eating or limiting unhealthy eating, PA attitude, subjective norm, perceived behavioral control, intention, and beliefs. The Theory of Planned Behavior constructs in the dynamic model of energy balance and behavior [13-17] inform individualized model-based interventions for each intervention participant. Participants complete online surveys daily at pre- and postintervention and during the open-loop phase, and daily and weekly during the intervention to assess their attitude, perceived behavioral control, subjective norm, intention to eat healthy and limit unhealthy eating, and participation in PA. Participants complete a one-time online survey at pre- and postintervention and monthly to assess their beliefs about eating healthy, limiting unhealthy eating, and participating in PA.Retrospective self-regulation for EI or healthy eating and PA [17]: Retrospective self-regulation in the dynamic model of energy balance and behavior [13-17] informs individualized model-based interventions for each intervention participant. Participants complete two 6-item online surveys daily at pre- and postintervention and during the open-loop phase, and weekly during the intervention to determine how good they are at regulating their EI or healthy eating and PA and how these behaviors impact GWG over the course of pregnancy.

#### Maternal Health

Participants complete the following measures at preintervention, during the intervention, and at postintervention:

Diet composition or quality and eating behaviors: Participants use the MyFitnessPal online app on 2 weekdays and 2 weekend days at pre- and postintervention, weekly during the first 2 weeks of the open-loop phase, and once a month during the intervention to assess their diet composition and quality. This information aids in personalized counseling of diet quality for the intervention group [19]. The Three Factor Eating Questionnaire [116,117] is completed at pre- and postintervention, weekly during the open-loop phase, and monthly during the closed-loop phase and is used to assess 3 dimensions of eating behaviors: dietary restraint (cognitive control of eating behavior), dietary disinhibition, and susceptibility to hunger.Sleep behaviors: The Pittsburgh Sleep Quality Index [127] assesses the quality and patterns of sleep and measures subjective sleep quality, sleep latency, sleep duration, habitual sleep efficiency, sleep disturbances, use of sleeping medication, and daytime dysfunction. The PROMIS Sleep Disturbance short-form survey [113] assesses difficulties and concerns with getting to sleep and staying asleep; evaluates the perceptions of the adequacy of and satisfaction with sleep; and measures sleep quality, sleep depth, and restoration associated with sleep. Participants also complete a daily self-report sleep log [128] to measure time to sleep and wake, minutes of sleep, nighttime awakenings, time spent awake after sleep onset, daytime naps, and daytime nap duration, and wear the Fitbit Charge 6 Activity Monitor [112] each night to assess time to sleep and wake, minutes of sleep, nighttime awakenings, and light and deep rapid eye movement sleep.

